## Abstract

Pediatric flat foot (PFF) is a very frequent entity and a common concern for parents and health professionals. There is no established definition, diagnostic method, or clear treatment approach. There are multiple conservative and surgical treatments, the implantation of foot orthoses (FO) being the most used treatment. The evidence supporting FO is very thin. It is not clearly known what the effect of these is, nor when it is convenient to recommend them. The main objective of this protocol is to design a randomized controlled trial to determine if personalized FO, together with a specific exercise regimen, produce the same or better results regarding the signs and symptoms of PFF, compared to only specific exercises. In order to respond to the stated objectives, we have proposed a randomized controlled clinical trial, in which we intend to evaluate the efficacy of FO together with strengthening exercises, compared to a control group in which placebos will be implanted as FO treatment along with the same exercises as the experimental group. For this, four measurements will be taken throughout 18 months (pre-treatment, two during treatment and finally another post-treatment measurement). The combination of FO plus exercise is expected to improve the signs and symptoms (if present) of PFF compared to exercise alone and the placebo FO group. In addition, it is expected that in both conditions the biomechanics of the foot will improve compared to the initial measurements.

## 1. Introduction

Pediatric flat foot (PFF) is a very frequent syndrome in primary care consultations, and it is also a shared concern among parents and professionals. Currently, there is no clear definition for the diagnosis of PFF, no treatment protocol, nor solid scientific evidence on the wide range of treatments [1,2].

PFF is characterized by a talocalcaneal misalignment, which is reflected as a collapse of the medial longitudinal arch (MLA) in a standing position [3]. Consequently, there is excessive pronation, accompanied by a drooping of the navicular. Some feet are also accompanied by calcaneal valgus [4]. All these alterations in the morphology of the foot force the rest of the structures, such as soft tissues or joints, to compensate for the excessive forces that act on the MLA [5]. These compensations cause an inefficient gait and symptoms such as pain, fatigue, stumbling when walking, problems in the proximal joints and reduced quality of life [6,7].

Diagnosis is based on clinical findings, including a variety of clinical tests and radiographic signs, these being considered the “gold standard” [6,8,9].

Regarding treatment, there are both conservative and surgical options, surgical being the last treatment option [10]. The most common conservative treatment is the use of foot orthoses (FO), where previous studies have concluded that they improve the results of some clinical tests, radiographic angles and symptomatology [11,12,13,14,15,16,17]. The purpose of the FO is to modify the position of the axis of the subtalar joint, decrease the speed of pronation, support the MLA and distribute loads more effectively [18,19]. Previous systematic reviews indicate that FO are beneficial and create positive changes in the development of the child’s foot [8,20,21]; these changes being greater in earlier ages of the treatment [22]. The exact age to start treatment is not clear, although it is recommended to start at preschool age (under 7 years old) so that the possibility of correcting the PFF is greater [23,24]. It has also been seen that the combination of FO with exercises is much more beneficial [25]. However, other studies indicate that the modifications that occur are those resulting from the natural development of the foot [26,27]. The evidence regarding the use of FO still does not present a consensus [20,28,29].

Therefore, there is a discrepancy between treating and not treating PFF. There are authors who conclude that it is not necessary, since the natural evolution of the foot is that the MLA begins to form at 3–4 years of age and ends at 10 years of age [26,27]. A recent meta-analysis [30] concludes that, due to the normal development of the foot, treatments should be ruled out unless there are symptoms such as pain, limited function or reduced quality of life. However, other authors recommend early treatment, based on the fact that flat feet persist in 23% of adults and may be associated with Achilles tendinopathy, plantar fasciopathy, tibial posterior tendinopathy, hallux rigidus, chondromalacia patellae or patello-femoral pain syndrome [1,2,7,13,20]. Based on these latest data, it would be unethical to leave these types of feet untreated. Additionally, a recent systematic review [24] demonstrated that FO are beneficial, with evidence regarding efficacy in treating signs and symptoms.

Therefore, since PFF is a very common syndrome which, if left untreated, could cause problems in the long term and there is no consensus on the treatment protocol, it is necessary to investigate the effectiveness of FO in terms of improvement of the signs and symptoms, including the prevention of pathologies or injuries and the improvement of the quality of life. Sagat, P et al. have shown that children with flat feet presented poor performance in certain physical tasks, in contrast to a control group with neutral feet [31]. In addition, since it is a subject of great interest for researchers, health professionals and parents, it is necessary to carry out an investigation to assess the effectiveness of FO, with a standardized diagnostic protocol with validated tests in a larger sample size than previously published studies and with a longer-term follow-up. Furthermore, as the authors Zhang J. et al. pointed out, early identification of PFF is necessary; thus an intervention plays a crucial role in enhancing the outlook. Also, there is an absence of consistent quantitative standards for diagnosing flexible flatfoot [32].

Therefore, the objective of the current study is to design a protocol for a randomized controlled trial (RCT) to determine whether personalized FO together with a specific exercise regimen produce the same or better results regarding the signs and symptoms of PFF, compared to only specific exercises. In addition, as specific objectives, to detect whether the possible bias that has prevented previous studies from demonstrating the efficacy of FO is due to the fact that these FO were not personalized; to define the PFF and to evaluate if there is a correlation between the clinical methods and the diagnosis and severity of the PFF.

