## 2. Materials and Methods

### 2.1. Study Design and Setting

The design is a randomized controlled two-arm trial.

Patients will be recruited from the university clinic from Universidad Católica San Antonio de Murcia, University of Malaga and schools nearby in Spain. They will be randomized to one of the two groups, each receiving a different intervention. The schedule to follow while carrying out this RCT can be found in Appendix A. The total period intended to be allocated to this study is from September 2023 to February 2025.

To randomize the sample, a Microsoft Excel spreadsheet will be used where a random assignment sequence will be generated. Each patient will be given a consecutive number in order of arrival and allocation concealed in envelopes.

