Once the FO have been provided, after assessing that it adapts well to the foot and does not cause discomfort, the patient will be requested to come in at 6 months. In the event that there is any discomfort or irritation to the child’s skin, an appointment will be made to readjust or modify the FO (in this visit the variables will not be evaluated, only the FO will be fixed; if there are no problems, this visit will not be carried out).

#### 2.3.2. Group 2

The participants will have the same intervention described for group 1, with the difference that they will use a placebo FO. This will be constructed using flat 1 mm 65 shore Ethylene-vinyl acetate (EVA), which will be cut to the foot size of the child and covered with the same top cover as the FO Group 1 to visually prevent them from being distinguished.

The instruments necessary for the development of this study and the budget necessary to carry out this clinical trial are included in Appendix D.

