## 3. Expected Results

Personalized FO along with a specific exercise regimen are expected to produce better results for signs and symptoms of PFF compared to specific exercises alone. In addition, it will be detected if the possible bias that has made the previous studies not demonstrate the efficacy of FO is that these FO were not personalized.

After the completion of this study, in which a large number of tests will be analyzed, the research will provide a definition of the PFF according to the common findings presented by the sample, a definition that nowadays is non-existent. Finally, we can evaluate if there is a correlation between clinical methods and the diagnosis and severity of PFF, in order to make an accurate diagnosis.

It is anticipated that the study will provide valuable evidence for improvement of the treatment of PFF, as well as for the diagnosis and management of this entity.

The main future research which is required after this protocol study is to carry out the detailed RCT described in the present manuscript. Also, qualitative research to understand the experience of patients with PFF wearing an FO is required.

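### The objective and expected result name exercise alone as the comparator, but the only control arm receives the same exercises plus a blinded flat placebo insole

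*Protocol article*

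**What the plan says.** Three places in the Protocol article name exercise alone as the comparator:

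- The Introduction (main objective) asks whether personalised FO with exercise "produce the same or better results regarding the signs and symptoms of PFF, compared to only specific exercises". The Abstract states the objective in the same terms.
- Section 3, Expected Results, says that FO with exercise "are expected to produce better results for signs and symptoms of PFF compared to specific exercises alone".
- The Abstract's expected result is worded "compared to exercise alone and the placebo FO group".

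Other places describe what is actually randomised:

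- Section 2.1: "The design is a randomized controlled two-arm trial".
- The Abstract, on the method: "compared to a control group in which placebos will be implanted as FO treatment along with the same exercises as the experimental group".
- Section 2.3.2, Group 2: "The participants will have the same intervention described for group 1, with the difference that they will use a placebo FO". The placebo is a flat 1 mm EVA insole cut to foot size, with the same top cover as the Group 1 device.
- Section 2.5: children and parents are blinded to allocation.

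Section 3.1, Limitations, mentions that there is no untreated control group. It does not mention that no group does the exercises without an insole.

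**The concern.** The comparator in the objective is not the comparator in the design. No child is allocated to exercise without an insole, so the trial does not directly estimate the contrast that the objective names.

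The main objective governs how the result will be reported, and parents and clinicians may well be choosing between exercise and exercise plus an orthosis. A result labelled as being against exercise alone would be taken to answer that choice. What the trial measures is whether a custom device does better than a flat one when both groups exercise. That is a sound question about FO-specific efficacy, but a different one.

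**Working it through.** No figure in the plan has to be reproduced for this point. It rests on setting the stated comparison beside the randomised one.

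**Notation.** Take any outcome, scored so that higher is better, and write its mean as:

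- F: custom FO plus exercise (Group 1)
- P: placebo FO plus exercise (Group 2)
- E: exercise with no insole (no group)

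**What is estimated and what is named.** The randomised contrast is F − P. The objective and Expected Results name F − E. The two are linked by

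F − E = (F − P) + (P − E).

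The trial has data on F and P and none on E, so P − E cannot be estimated. Reading F − P as F − E amounts to setting P − E = 0.

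**Is P − E = 0 stated or supported?** It is not stated. The article calls the insole a placebo but does not argue that wearing one is the same as wearing none. Group 2 has the same intervention as Group 1 apart from the device, so it also has things that come with an insole:

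- Blinding and the matching top cover (Sections 2.5 and 2.3.2) mean that both arms share any expectation of benefit. Pain on a visual analogue scale is among the outcomes (Section 2.4.2).
- Appendix C asks for daily wear for as many hours as possible, Section 2.5 has the device checked after a month, and Section 3.1 has its use followed up by phone. Without an insole there would be nothing to wear, check or follow up.
- Section 3.1 ties orthosis use to closed shoes, and Appendix C treats footwear as part of the treatment. Wearing an insole may therefore change the shoes worn.

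These are reasons not to take P − E = 0 for granted. They do not show that P − E is large, and the article gives no figure from which to size it.

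**What each value of P − E would mean.**

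| P − E | Trial finds F − P > 0 | Trial finds F − P = 0 |
|---|---|---|
| zero | F − E = F − P; the stated comparison holds | F − E = 0; the stated comparison holds |
| positive | F − E exceeds F − P; superiority over exercise alone holds, and the estimate is conservative | F − E = P − E > 0; reading the result as no gain over exercise alone would be wrong |
| negative | F − E is smaller than F − P; superiority over exercise alone does not follow automatically | F − E < 0; reading the result as equal to exercise alone would be wrong |

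The null column matters because the objective asks about results that are the same or better, so a finding of no difference is one of the outcomes it provides for.

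**Sample size.** Section 2.6 sizes two groups, 84 + 84 = 168 after allowance for losses. Naming the comparator correctly leaves the number of groups, the allocation and this total as they are.

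**The case against.** The case against runs as follows. Calling a placebo-controlled add-on trial a test of treatment plus background against background is common shorthand, and it presumes an inert placebo. The article calls the insole a placebo, makes it flat and 1 mm thick, and nowhere says that it treats anything. The Abstract and Section 2.3.2 describe the control arm correctly, so a careful reader is not misled about the design. Most outcomes are measured by an examiner (foot posture, heel position, navicular drop, arch index), and pain is not required for entry, so expectation would bear mainly on a small part of the outcome list.

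Much of this stands. Placebo control is a good choice here, and the effect of the insole itself may be small for the measured angles and indices. It does not remove the mismatch: the inert-placebo assumption is left unsaid, and the objective and Expected Results name a group that does not exist.

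A reader might also infer stronger things that the documents do not support:

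- **A third, exercise-only arm.** The Abstract's phrase "is expected to improve the signs and symptoms (if present) of PFF compared to exercise alone and the placebo FO group" could suggest two comparators. But the Abstract defines a single control group shortly before, its next sentence speaks of both conditions, Section 2.1 says two arms and Section 2.6 sizes two groups. The phrase is best read as a clumsy name for the one control arm.
- **No conclusion against exercise alone could ever be drawn.** If the insole is inert or mildly helpful, a positive result carries over.
- **The article has committed itself to a false null conclusion.** It expects superiority and nowhere states that FO are no better than exercise.
- **A known percentage bias.** Any such figure would rest wholly on assumed effects.

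**Conclusion.** The point holds as an error of wording in the main objective and the expected result. The randomised contrast is custom FO against placebo FO, both with exercise, and it is not the contrast named. The difference between the two is the effect of the placebo insole and what comes with it. The documents do not quantify that effect, and it could be zero.

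The practical risk is uneven. If the effect is zero or favourable, a positive result is safe and possibly conservative. A null result is the exposed one: it would show that custom shaping adds nothing detectable over a flat insole, not that an insole adds nothing to exercise. The design itself is not at fault.

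**What to change.** - **Abstract (objective and expected result), Introduction (main objective) and Section 3:** replace each exercise-only comparator, and the ambiguous double comparator in the Abstract's expected result, with *the same exercises plus a flat placebo insole*.
- **Section 3.1:** add a sentence such as *The trial does not estimate the effect of FO plus exercise compared with exercise without an insole.*

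The cost is a few words in four places and one added sentence. Arms, outcomes, analysis and sample size stay as they are.

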### 2.3. Interventions

At the first visit, parents will be informed of their child’s current problem, treatments, and the existence of this study. In the case of accepting to participate in the study, the process will begin: all the variables will be carefully collected, the treatment will be established and an appointment will be made for follow-up at 6 months.

First, all the affiliation data will be collected and the PFF will be diagnosed.

#### 2.3.1. Group 1

For custom insoles, a mold will be taken using phenolic foam. To do this, the child will be asked to sit in a chair (to take the mold semi-load baring). The mold will be taken in a corrected position, that is, limiting the internal rotation of the tibia with one hand and the windlass mechanism will be performed to increase the MLA. The mold must remain neutral, so in the event that a varus or valgus print has emerged, this process will be repeated. Once we have the mold filled with plaster, two modifications will be made: a moderate medial heel skive (5 mm and an angulation of 15°) in the hindfoot and a slight inversion balance of 4° in the forefoot. Once the mold is prepared, the FO will be thermoformed; for this, we will use a 3 mm polypropylene, 25 Shore-A EVA as lining and 65 Shore-A EVA to stabilize the hindfoot.

In addition, the exercises to be performed will be explained to them and they will be given all the recommendations regarding the performance of exercises, the use of FOs and shoe therapy. These explanations will be provided in an additional report (Appendix C) that will be given to all subjects together with a calendar so that they write down all the days they perform the exercises with an X.

The exercises will first be explained by the podiatrist to the child and the parent/legal guardian. In addition, a standard video will be created so that the child can see it, in which the exercises will be explained through drawings in order to capture the attention of the child. The parent/legal guardian needs to confirm that the child is doing it correctly.

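### Two specific objectives, personalisation as the reason earlier trials failed and a definition of PFF with correlation to diagnosis, have no contrast in this two-arm, cases-only design

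*Protocol article*

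**What the plan says.** The last paragraph of the Introduction sets the objectives. The main one is to determine whether personalised FO with exercise "produce the same or better results regarding the signs and symptoms of PFF, compared to only specific exercises". One specific objective is to establish if a "possible bias that has prevented previous studies from demonstrating the efficacy of FO is due to the fact that these FO were not personalized". Another is "to define the PFF and to evaluate if there is a correlation between the clinical methods and the diagnosis and severity of the PFF". Section 3 (Expected Results) repeats both specific aims as outputs of the trial. It says the personalisation question will be resolved, and that "the research will provide a definition of the PFF according to the common findings presented by the sample".

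The design sections read as follows.

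- Section 2.1: "The design is a randomized controlled two-arm trial".
- Section 2.3, Group 1: "For custom insoles, a mold will be taken using phenolic foam"; the exercise programme is given as well.
- Section 2.3, Group 2: "The participants will have the same intervention described for group 1, with the difference that they will use a placebo FO", made from flat 1 mm EVA under the same top cover.
- Section 2.2: a child is eligible only if diagnosed with PFF by preset limits on Foot Posture Index (FPI), navicular drop, relaxed calcaneal stance position (RCSP), pronation angle, arch index, heel rise and windlass.

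On comparators, section 3.1 (Limitations) acknowledges only the lack of an untreated group.

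**The concern.** An objective can be answered only if the design contains the comparison it needs. To attribute earlier null results to lack of personalisation, personalised and non-personalised orthoses must be compared. To define a condition, or to relate tests to its diagnosis, some children must be without it. The article describes neither, yet states both answers as expected results.

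At stake is what the trial may conclude. A positive result could be published as an explanation of other trials that was never tested. A list of features common among selected children could be published as a diagnostic definition. The article itself says that no accepted definition exists, so others might adopt such a definition. No analysis plan can repair this, because it cannot supply a missing arm or missing non-PFF children.

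**Working it through.** The article gives no figure for these objectives, so there is none to reproduce. The sample size in section 2.6 has no part in this point. The check sets each objective against the design.

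| Objective (Introduction, section 3) | Contrast needed | What sections 2.1 to 2.3 supply |
|---|---|---|
| Lack of personalisation explains earlier failures | Personalised versus non-personalised functional FO | Custom FO versus flat placebo FO, both with exercise |
| Correlation of clinical methods with diagnosis | Children with and without PFF | Children with PFF only |
| Definition of PFF from common findings | Evidence that findings distinguish PFF from non-PFF | Findings in PFF only |
| Correlation with severity | Spread of severity | Spread among cases, cut by the entry limits |

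**Personalisation.** The randomised difference estimates the effect of a custom orthosis over a flat insole. A positive result would be equally compatible with any arch-supporting device working. Setting it beside earlier trials would be a non-randomised comparison, confounded by age, entry criteria, exercise and follow-up.

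**Diagnosis and definition.** Diagnosis takes one value in the sample, so its variance is zero and its correlation with any test is undefined. Two of the seven entry tests (heel rise and windlass) are fixed at baseline by eligibility. The others are truncated. FPI above 6 leaves 7 to 12, so the normal and supinated classes of section 2.4.1 are empty at baseline. RCSP is bounded on both sides (6° to 12°), which also removes the more extreme values. A common finding on any of these seven partly restates the entry limits. For tests outside the entry list, a common finding shows how often it occurs in PFF but not whether it is rarer elsewhere.

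**Severity correlations, illustration only.** The article does not say what share of children the entry limits select. Assume a normal trait with only the top 20% enrolled.

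- Cut-off c = 0.8416; normal density there 0.27996; λ = 0.27996/0.20 = 1.3998.
- Variance ratio u² = 1 + cλ − λ² = 1 + 1.1781 − 1.9594 = 0.2187, so u = 0.468.
- r′ = r·u / √(1 − r² + r²u²).
- r = 0.6: 0.281/√(0.64 + 0.0787) = 0.281/0.848 = 0.331.
- r = 0.8: 0.374/√(0.36 + 0.1400) = 0.374/0.707 = 0.529.

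Simulation of a bivariate normal (2,000,000 draws) shows how the result depends on the assumed cut-off, and on whether one or both measures are selected on:

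| True r | Selected on one: top 30% / 20% / 10% | Selected on both: top 30% / 20% / 10% |
|---|---|---|
| 0.3 | 0.16 / 0.15 / 0.13 | 0.11 / 0.09 / 0.07 |
| 0.5 | 0.28 / 0.26 / 0.23 | 0.22 / 0.19 / 0.16 |
| 0.7 | 0.45 / 0.42 / 0.37 | 0.40 / 0.36 / 0.32 |

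Attenuation appears in every cell, but its size depends on the assumption. Actual selection is joint on seven criteria, one of them two-sided, so none of these figures is an estimate for this trial.

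**The case against.** The strongest defence is that the treatment question, which is the reason for randomising, is answerable, and that the rest is loose phrasing. Much of this stands, and it rules out several stronger readings.

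- *The comparator is wrong.* The abstract expects improvement "compared to exercise alone and the placebo FO group", and a reader might infer a missing third arm. The documents do not support that. The abstract itself describes a control group with placebo FO and the same exercises, and section 2.1 gives two arms. A flat 1 mm insole approximates exercise alone if it is close to inert. This is a matter of wording.
- *'Same' will be read from a non-significant test.* The article never says so. Section 3 expects better results and section 2.7 tests for a difference. A non-inferiority margin could sit in a plan that is not shown.
- *A null result could not exclude a moderate difference.* Too absolute. With 84 × 0.70 ≈ 59 completers per group, the 95% half-width is 1.96 × √(2/59) = 0.36 SD. An estimate near zero would exclude 0.5 SD.
- *The definition is purely circular.* Not so. Supination resistance, subtalar axis, Beighton scale, Chippaux-Smirak index, navicular height and others (sections 2.4.1 and 2.4.2) are not entry criteria, and their frequencies are not fixed directly by selection. The lasting problem is the lack of non-PFF children.
- *Severity cannot be studied.* It can. Eligible children still span the pronated and highly pronated FPI classes, so range restriction weakens these correlations without making them meaningless.

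None of this supplies a contrast for personalisation or for diagnosis.

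**Conclusion.** The point holds for two specific objectives. The personalisation objective has no randomised contrast. The aims of defining PFF and correlating tests with its diagnosis have no non-PFF children to work with. Both conclusions follow from the stated arms and eligibility criteria and need no numerical assumption. Correlations with severity remain legitimate as description within cases. They will probably understate the relations in children generally, by an amount that cannot be derived from the article; 0.6 falling to about 0.33 and 0.8 to about 0.53 rests on an assumed top-20% selection on a single normal trait.

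The phrases about exercise alone and 'same or better' need only wording alignment. A reader might infer that the trial as a whole is invalid. It is not: custom FO plus exercise against placebo FO plus exercise remains a proper randomised comparison. The correction should be made, because otherwise the plan leads to conclusions that the data cannot support.

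**What to change.** 1. Delete the personalisation objective from the Introduction and the matching sentence from section 3.
2. Drop the aims of defining PFF and correlating methods with diagnosis, together with the promised definition in section 3.
3. Keep the severity correlations, labelled as descriptive within children meeting the entry criteria. Alternatively, compute them on all screened children, with consent, including those who fail the criteria.
4. For consistency, state the main objective in the abstract, Introduction and section 3 as superiority of custom FO plus exercise over placebo FO plus exercise. Remove 'same or' and the references to exercise alone as a comparator.

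The cost is narrower claims and editing in three places. No arm, patient or measurement is added to the trial. The optional analysis of screened children needs consent from their guardians and the relevant tests recorded in those who turn out ineligible. The randomised comparison and its analysis stay as planned.
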